### Sample size estimation

2.15

Like the other pilot study, we calculated that 15 participants are required in each group, giving a total of 45 participants, in this clinical trial. A 25% of dropout rate was taken into consideration for a sample size of 12 per group.^[25]^ The CRC will manage the treatment schedule of subjects to minimize the dropout rate.

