### Study design

2.1

This study is a randomized controlled clinical trial with a prospective, outcome assessor-blinded, parallel-arm, 1:1:1 allocation ratio, single-center design. This study is a pilot study comparing the effect between “EA with computerized cognitive rehabilitation” and “tDCS with computerized cognitive rehabilitation” to investigate the effect and safety of combination therapy of EA or tDCS with computerized cognitive rehabilitation. Participants who meet the inclusion and exclusion criteria will be randomly allocated into a computerized cognitive rehabilitation treatment (CCRT) group (n = 15), combination therapy with EA and computerized cognitive rehabilitation treatment (CECCRT) group (n = 15), and combination therapy with tDCS and computerized cognitive rehabilitation treatment (CTCCRT) group (n = 15), for a total of 45 participants. The CCRT group will receive computerized cognitive rehabilitation therapy, the CECCRT group will receive combined EA and computerized cognitive rehabilitation therapy, and the CTCCRT group will receive combined tDCS and computerized cognitive rehabilitation therapy. All groups will receive therapy once a day for 3 days a week (excluding Saturdays and Sundays) for 8 weeks, giving a total of 24 therapies scheduled during the hospitalization period at Chonnam National University Hospital.

The outcomes will be measured before intervention, at the end of intervention, 8 weeks after the first intervention, and 4 weeks after completion of the intervention. The change in cognitive function as assessed using the Lowenstein occupational therapy cognitive assessment (LOTCA) scale will be measured as the primary outcome. The changes in the performance of every day movements will be measured using the Korean version of the modified Barthel index (K-MBI) and changes in health-related quality of life will be measured using the European Quality of Life Five Dimension Scale (EQ-5D-3L). The K-MBI and EQ-5D-3L will be secondary outcomes in this study.

This clinical trial was conducted by the Korea Health Industry Development Institute in 2018, a research project on the development of therapeutic techniques for the prevention of dementia and combination therapy with computerized cognitive rehabilitation (HI18C0546).

The design of this study is summarized in Figure 1. And time table of protocol is summarized in Table 1.

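### Sample size: 15 per group with 25% dropout leaves about 11 per group, not the 12 stated

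*Protocol article*

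**What the plan says.** Section 2.15 (Sample size estimation) of the protocol article opens by referring to pilot precedent ("Like the other pilot study") and continues: "we calculated that 15 participants are required in each group, giving a total of 45 participants, in this clinical trial". The next sentence gives the allowance for loss: "A 25% of dropout rate was taken into consideration for a sample size of 12 per group", followed by a literature reference. The article shows no inflation formula and gives no effect size, standard deviation or power.

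The 15 per group is repeated in Section 2.1 (Study design) and Section 2.6 (Randomization). The total of 45 also appears in the Abstract and in Section 2.1 ("for a total of 45 participants"). The 12 and the 25% appear only in Section 2.15.

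**The concern.** Section 2.15 links three figures: the number randomised per group (15), the expected loss (25%) and the group size for which that loss is allowed (12). Any two of them determine the third, and the printed three do not fit. The pattern is that of a common slip, in which the target is multiplied by one plus the dropout rate instead of being divided by one minus the dropout rate.

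What is at stake is modest. Twelve is the only target below 15 that the article gives, so readers will take it as the number expected to remain per group. If 25% is the loss the investigators expect, that number is too high. If 12 is what they expect to keep, the dropout rate is misstated. As printed, a reader cannot tell which figure is meant.

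**Working it through.** **Inputs, all from the protocol article**

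- Randomised per group, n = 15; total 45 (Sections 2.15 and 2.1)
- Dropout rate, d = 25% (Section 2.15)
- Group size for which dropout is allowed, m = 12 (Section 2.15)
- Three groups, equal allocation (Section 2.1)

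**Step 1: reproduce the printed figure.** m × (1 + d) = 12 × 1.25 = 15 per group, and 3 × 15 = 45. This matches exactly, so the 15 appears to be 12 increased by a quarter of itself.

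**Step 2: the number needed to keep 12.** If d is the share of randomised participants lost, then n × (1 − d) = m, so n = m/(1 − d) = 12/0.75 = 16 per group, and 3 × 16 = 48 in total. The quotient is exactly 16, so rounding cannot turn it into 15.

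**Step 3: what 15 per group delivers at 25% dropout.** 15 × 0.75 = 11.25 per group, and 45 × 0.75 = 33.75, about 34 in total. The implied figure is 3 × 12 = 36. The expected shortfall is 0.75 per group and 2.25 in total.

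**Step 4: the dropout rate that fits 15 and 12.** 1 − 12/15 = 0.20, that is 20%.

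**Step 5: chance of reaching 12.** Assume that participants drop out independently, each with probability 25%. A given group of 15 then keeps at least 12 with binomial probability 46%. A group of 16 does so with probability 63%.

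**Step 6: effect on precision, for illustration only.** For a single unadjusted comparison of two groups with a common SD, the 95% confidence interval half-width in SD units is t × √(2/m), with 2m − 2 degrees of freedom.

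| Remaining per group | Half-width (SD) |
|---|---|
| 12 | 0.847 |
| 11 | 0.889 |

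The ratio is 0.889/0.847 = 1.05, so the interval is about 5% wider at 11 than at 12.

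**The case against.** The strongest defence is that the allowance was meant as 25% of the 12, that is three extra participants per group, which gives 15 exactly. The sentence is loose enough to have been written with that in mind, and this is probably how the figure arose. It does not rescue the text. A dropout rate is normally the share of those enrolled who are lost, Section 2.15 does not define it otherwise, and on that meaning three lost from 15 is 20%.

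The second defence is that the discrepancy is too small to matter. Much of this stands. The gap is under one participant per group, no stated operating characteristic depends on 12, and no design decision changes. That makes it a small correction, but the figures as printed are still wrong.

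A reader might go further and infer that the words used for 15 ("we calculated that 15 participants are required in each group, giving a total of 45 participants") claim a power calculation that the trial lacks, or that the hope in the Discussion of finding the combinations safe and effective rests on this sample size. The document does not support that. Section 2.15 gives the pilot basis in the same sentence, Section 2.1 calls the trial a pilot, and the Discussion names the small sample as a limitation. Power is claimed nowhere, and the Discussion sentence is an expectation about results, not a statement about sample size. Nor can one say that nothing lies behind the 12: a reference is cited that is not at hand, and the article condenses a fuller protocol.

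**Conclusion.** The figures in Section 2.15 are inconsistent. With 15 randomised per group and 25% dropout, about 11 per group (11.25; about 34 in total) are expected to remain, against 12 per group (36 in total) as stated. Keeping 12 at that rate would take 16 per group.

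This rests on one assumption, that the dropout rate is the share of randomised participants lost. The 46% and 63% also assume independent dropout at exactly 25%. The half-widths assume one unadjusted two-group comparison. Section 2.17 lists several analyses for three groups without singling out such a contrast, so the half-widths show scale only.

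It would be wrong to conclude that the trial is underpowered against its own plan or that the design fails. The article states no power, effect size or precision target, and the change in precision is about 5%. What needs correcting is a misstated allowance for dropout.

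**What to change.** Keep 45 participants and correct the sentence in Section 2.15 in one of two ways:

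- 15 per group allows for 20% dropout to leave 12 per group; or
- with 25% dropout, about 11 per group (about 34 in total) are expected to remain.

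The choice depends on which figure the investigators believe, the 25% or the 12. Either version leaves Sections 2.1 and 2.6 and the Abstract unchanged. The cost is one sentence and a slightly less favourable statement: a smaller tolerance for dropout in the first version, a smaller remaining group in the second.

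Randomising 16 per group (48 in total) would also make the figures agree, at the cost of three more participants. It is not needed, because no stated power or precision depends on reaching 12, and the Discussion cites limited funds as the reason for the sample size.

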### Data management

2.16

The participants in this study will be required to voluntarily sign the consent form before beginning this protocol; the data will then be collected. All data from this study will be recorded and documented or recorded in Excel files by the CRC and all collected data will only be used for research purposes. Personal data including name and resident registration number will not be recorded or used. For data security, all data will be secured in a double locked cabinet until the end of this study and will only be accessible by investigators. Investigators who monitor the data include the principal investigator, resident in charge of EA, occupational therapist in charge of CCRT, doctor in charge of tDCS, and the CRC.

### Statistical analysis

2.17

The statistical analysis will be conducted by a statistician who is not involved in this study and SPSS version 21 software (IBM Corp, Armonk, NY) will be used. We will analyze the general characteristics and outcome data at baseline, at the end of the intervention, and 4 weeks after intervention completion. Continuous variables will be presented as means and standard deviations or means and 95% confidence intervals. Independent *t*-test or Wilcoxon rank sum test will be used for continuous data and chi-squared test or Fisher exact test will be used for categorical data. The primary and secondary outcomes of the 3 groups will be measured using the changes in score at the end of the intervention and 4 weeks after the end of the intervention relative to the initially evaluated score. Each group will then be analyzed using a paired *t*-test or Wilcoxon signed rank test. A repeated measures analysis of variance, 2 sample *t*-test, Wilcoxon rank sum test can be used for the analysis of the degree of change at each outcome evaluation period. *P*-values <0.05 will be considered statistically significant.

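### If classical repeated measures ANOVA is used for LOTCA, anyone missing the last visit loses an observed 8-week score; a mixed model would keep it at almost no cost

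*Protocol article*

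**What the plan says.** Section 2.17 (Statistical analysis) uses three assessments, "at baseline, at the end of the intervention, and 4 weeks after intervention completion", and names "SPSS version 21 software" without naming a procedure. It defines the outcome as change from baseline: "The primary and secondary outcomes of the 3 groups will be measured using the changes in score at the end of the intervention" and again 4 weeks later. For the degree of change at each evaluation it lists "A repeated measures analysis of variance, 2 sample" t-test and Wilcoxon rank sum test. The wording is permissive: any of the three may be used, and none is named as the primary analysis. Paired tests are listed for change within each arm.

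Section 2.15 (Sample size estimation) allows for attrition: "A 25% of dropout rate was taken into consideration for a sample size of 12 per group", with 15 per arm and 45 in total. It does not say when dropout is expected. Section 2.8 (Blinding) states that participants know their treatment. Section 2.10 (Outcome measurements) separately excludes anyone with fewer than 20 of the 24 sessions.

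**The concern.** The article expects dropout and then lists, as its only longitudinal method, one that in classical form (SPSS GLM Repeated Measures) uses complete cases only. It is also the only listed method for change scores that compares all three arms together, so it is a natural choice for the main analysis.

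If it is chosen, someone who completed all 24 sessions and the 8-week assessment but missed the last visit leaves the analysis altogether. The 8-week comparison then rests on fewer people than were measured, selected by whether they returned 4 weeks after treatment ended.

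The two-sample alternatives avoid this at 8 weeks. At follow-up they use only those who returned, and the 8-week score of a non-returner does not inform the estimate. None of the three uses baseline LOTCA as a covariate; baseline enters only by subtraction or as another repeated measure. In a trial of 45, measured primary data should not be lost through the choice of procedure.

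**Working it through.** **Inputs.** From section 2.15: 15 per arm, 12 per arm after dropout, 25% dropout. From section 2.17: three visits. Assumed, because the article does not give it: f, the share of dropouts who leave after the 8-week visit, varied from 0 to 1.

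**The article's own figure.** 12 × 1.25 = 15 per arm, or 45 in total, matches. Dividing by the retained share gives 12 / 0.75 = 16. So 15 to 12 is a loss of 1 − 12/15 = 20%, while 25% of 15 leaves 15 × 0.75 = 11.25. Both readings are carried forward.

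**Observed 8-week scores deleted.** With dropout d:
- complete cases per arm = 15(1 − d)
- 8-week scores observed per arm = 15(1 − d(1 − f))
- scores deleted per arm = 15·d·f
- ratio of standard errors for the 8-week difference = √(observed / complete)

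| f | Deleted per arm, d = 20% | SE ratio | Deleted per arm, d = 25% | SE ratio |
|---|---|---|---|---|
| 0 | 0 | 1.000 | 0 | 1.000 |
| 0.25 | 0.75 | 1.031 | 0.94 | 1.041 |
| 0.50 | 1.50 | 1.061 | 1.88 | 1.080 |
| 0.75 | 2.25 | 1.090 | 2.81 | 1.118 |
| 1 | 3.00 | 1.118 | 3.75 | 1.155 |

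Over three arms the maximum is 3 × 3 = 9 of 45, or 3 × 3.75 = 11.25 of 45.

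**Bias at 8 weeks, by simulation.** Two arms of 15, no true difference, 25% lost, all of it after week 8, 20,000 runs. The complete-case error in the 8-week difference, in SD units, was:
- random dropout: 0.00
- poor responders leave more often, equally in both arms: 0.00
- poor responders leave more often in one arm, random dropout in the other: about 0.22
- opposite directions in the two arms: about 0.43

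With all 8-week scores kept it was 0.00 in every case.

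**Bias at both times, with timing varied.** 15,000 trials per scenario, 25% lost by the last visit, assumed correlations of 0.7 (baseline with each follow-up) and 0.8 (between follow-ups). In one arm, late dropouts came only from those below the median 8-week change. For f = 0.25, 0.50 and 1, the complete-case error was 0.050, 0.105 and 0.204 baseline SD at 8 weeks, and 0.032, 0.069 and 0.137 at follow-up. A regression estimate using the 8-week score, standing in for the mixed model, had error of at most 0.005. If dropout is monotone, the follow-up error applies equally to the two-sample tests, because they use the same returners.

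**Baseline adjustment.** With equal variances and baseline correlation ρ, the variance of an adjusted comparison relative to a change-score comparison is (1 − ρ²) / (2(1 − ρ)) = (1 + ρ)/2, which is below 1 for any ρ below 1. At the assumed ρ = 0.7 it is 0.51/0.60 = 0.85, before the small cost of estimating the slope.

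**The case against.** A reader might infer that the plan does discard 8-week primary data and that its arm comparison is biased. The article does not support that.

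- The ANOVA is one of three permitted methods. A two-sample comparison of change at 8 weeks keeps everyone seen at that visit, so the whole 8-week precision gain in the table is available within the article's own list.
- Only the software package is named. SPSS also has a MIXED procedure that accepts incomplete cases.
- Dropout timing is not given. Sections 2.10 and 2.13 remove people for low attendance or adverse events, which points to losses during treatment. If all dropout precedes week 8, nothing is deleted.
- The bias figures need non-return that depends on outcome and differs by arm. The only support for that is open treatment, and all three arms receive active treatment.
- In the simulations, dropout depended only on the observed 8-week change. That is missing at random, so the near-zero error of the likelihood-type estimate is built in. It would not be guaranteed if non-return depended on unobserved follow-up status.
- A rule for missed visits may sit in an analysis plan or full protocol not shown, so the absence of one here is not a fault.

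All of this stands, and it limits the point to a conditional one. Two things remain. The one listed method that handles the visits jointly can delete observed scores. No listed between-arm method uses the 8-week score at follow-up or adjusts for baseline.

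**Conclusion.** The point holds conditionally. If classical repeated measures ANOVA is chosen, between none and 3 observed 8-week LOTCA scores per arm are lost at 15 to 12 per arm, with the 8-week standard error up to about 12% larger. At 25% of 15, the loss is between none and about 4 per arm, with the standard error up to about 15% larger. Where the truth lies depends wholly on the unstated timing of dropout.

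Bias is possible but not established: it is zero under random or arm-symmetric dropout. The simulated 0.03 to 0.43 SD holds only for the assumed mechanisms, all at 25% loss. The under-20-session exclusion is a more certain source of selection after randomisation and is a separate matter. What justifies a change is that a better method is available in the named software and uses data already collected.

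**What to change.** In section 2.17, name as the between-arm analysis a linear mixed model (SPSS MIXED, REML) with arm, visit, arm-by-visit and baseline LOTCA, and unstructured within-person covariance. Use every observed post-baseline LOTCA score, so that a participant who misses one follow-up visit stays in with the other. Report the arm contrasts at the end of intervention and 4 weeks after. Use the same model for K-MBI and EQ-5D-3L.

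Reconcile the analysis population with the under-20-session exclusion in section 2.10. If the model is meant to include all randomised participants, the two statements conflict and one must give way.

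The cost is a short rewording and slightly more analysis work, with no new data, visits or participants. The small downside is that the model assumes data are missing at random, which is weaker than what a complete-case ANOVA needs but still cannot be verified from the data.

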## Discussion

3

This protocol is designed to explore the synergistic effect of combined EA and CCRT therapy in the treatment and prevention of cognitive impairment caused by cerebrovascular disorders. In this protocol, we follow the Recommendations for Interventional Trials (SPIRIT) and Consolidated Standards of Reporting Trials (CONSORT) 2010 guidelines.^[26]^ For the evaluation of each therapy, the outcome measurements include the LOTCA, K-MBI, and EQ-5D-3L. The LOTCA is one of the most commonly used qualitative tools in the evaluation of cognitive function in cerebrovascular disease. Therefore, we will use changes in the LOTCA scale as the primary outcome, with changes in the K-MBI and EQ-5D-3L scores as secondary outcomes. Through this clinical trial, we expect to find that EA or tDCS with CCRT is safe and effective for patients with VCI.

This protocol has some limitations. First, we cannot perform a double blinded study because the practitioners know which procedure is applied to which participant. Second, we cannot use a multi-center pilot study and large sample size design due to the limited research funds. Third, we cannot apply another procedure other than EA and tDCS due to the small sample size and lack of adequate preliminary studies.
